## Abstract

**Background:**

The ISAR study is a prospective, longitudinal, observational cohort study to improve the cardiovascular risk stratification in endstage renal disease (ESRD). The major goal is to characterize the cardiovascular phenotype of the study subjects, namely alterations in micro- and macrocirculation and to determine autonomic function.

**Methods/design:**

We intend to recruit 500 prevalent dialysis patients in 17 centers in Munich and the surrounding area. Baseline examinations include: (1) biochemistry, (2) 24-h Holter Electrocardiography (ECG) recordings, (3) 24-h ambulatory blood pressure measurement (ABPM), (4) 24 h pulse wave analysis (PWA) and pulse wave velocity (PWV), (5) retinal vessel analysis (RVA) and (6) neurocognitive testing. After 24 months biochemistry and determination of single PWA, single PWV and neurocognitive testing are repeated. Patients will be followed up to 6 years for (1) hospitalizations, (2) cardiovascular and (3) non-cardiovascular events and (4) cardiovascular and (5) all-cause mortality.

**Discussion/conclusion:**

We aim to create a complex dataset to answer questions about the insufficiently understood pathophysiology leading to excessively high cardiovascular and non-cardiovascular mortality in dialysis patients. Finally we hope to improve cardiovascular risk stratification in comparison to the use of classical and non-classical (dialysis-associated) risk factors and other models of risk stratification in ESRD patients by building a multivariable Cox-Regression model using a combination of the parameters measured in the study.

**Clinical trials identifier:**

ClinicalTrials.gov NCT01152892 (June 28, 2010)

## Background

Chronic kidney disease, in particular ESRD is associated with a very high cardiovascular morbidity and mortality [1]. As access to dialysis is getting easier and the spectrum of patients suitable for dialysis has broadened, the worldwide use of renal replacement therapy (RRT) is expected to rise significantly in the next years [2]. The life expectancy of ESRD is similar to metastatic cancer disease. For example the overall life expectancy of a patient after initiation of dialysis is 8 years in the age group of 40 to 44 years, compared to 30 to 40 years of life expectancy in the general population [3]. Despite recent advances in the field of dialysis technique [4] and insights into the complex pathophysiology [5] of the changes in ESRD patients, we are far from understanding the disease and even further from having a cure. To understand the complex processes happening in ESRD, we need a comprehensive characterization of the cardio- and cerebrovascular system as the major events and causes of mortality are of cardio-/cerebrovascular nature. Based on these findings we hope to gain a better insight into the pathophysiological processes happening in ESRD and to identify new risk factors and improve risk stratification. With introducing the ISAR study we try to shape the most complex cardiovascular image of the patient, which can be derived from easy and inexpensive measurements. Thus, the methods used in this study could be easily adapted for routine use in dialysis centers worldwide. Overall, we want to establish a cohort that reflects the current medium age of dialysis patients in western countries, as we know that dialysis patients get older. Previous studies included patients roughly 10 years younger than the patients we treat today and no special consideration of particular habitats were reported. Here we report the rationale and the study design of the ISAR study. We describe (1) cross-sectional and prospective study objectives, (2) the methods that will be used in the study and (3) the rationale for choosing these methods.

### Study objectives

Therefore, we aim to (1) record a cross-sectional and longitudinal picture of the vascular bed to identify and follow changes in the vasculature and (2) to improve cardiovascular (CV) and non-cardiovascular (non-CV) risk stratification by following the patients for up to 72 months and recording events. We intend to establish an end stage renal disease cohort of more than 500 patients in Munich city and surrounding area (urban vs. rural) to get an idea of the dialysis patients treated today in Germany which should be comparable with large parts of Europe.

The main goals of the ISAR study are:A cardio/-cerebrovascular characterization of a representative ESRD cohort (cross-sectional and longitudinal)To find associations between novel and established risk factors and cardiovascular disease to get a better mechanistic insight into the pathophysiology of cardiovascular and infectious disease in dialysis patientsTo follow cardiovascular changes over time (arterial stiffness, central hemodynamics, cardiovascular events)To find new and established risk factors for the prediction of morbidity and mortality (cardiovascular, non-cardiovascular (dialysis-associated))To find associations between neurocognitive scores/testing and end organ damage, cardiovascular risk factors and vascular parametersTo establish a serum sample database for the discovery of novel biomarkers in ESRDTo develop a robust model to predict cardiovascular morbidity and mortality and death of all causes in a multivariable Cox-regression analysis

We focus on the above mentioned objectives as we have identified them as improvable areas of interest in previous landmark studies, because the problem has either (1) not been addressed before, (2) the population was too small or (3) the baseline characteristics/epidemiology of the population has changed over time, so it is not representative for the actual population of dialysis patients taken care of in dialysis centers in western countries any longer. Furthermore, we seek to develop a combined model of the different risk stratification methods (ABPM, PWA, PWV, autonomous dysfunction, RVA) to improve prediction of cardiovascular and non-cardiovascular events.

In the following, we give an overview of research questions that we want to address after establishment of the planned dataset.

### Ambulatory and office/dialysis blood pressure monitoring (ABPM)

Objectives with cross-sectional resultsBuild a 24-h ABPM reference database for a well-defined dialysis cohort of prevalent dialysis patients that are comparable to the current dialysis population treated in European countriesEvaluate the incidence of masked, white coat hypertension and dialysis treatment associated hypertension by comparison of pre- and post-dialysis BP measurements with ABPM recordingsEvaluate the frequency of nocturnal hypertensionFind associations between 24-h ABPM measurements and target organ damageFind associations between 24-h ABPM measurements and other cardiovascular parameters e.g. retinal vessel diameter, autonomic dysfunction, central hemodynamics and cardiovascular risk factorsEvaluate the adherence of dialysis patients to the prescription of 24-h ABPM (% unwillingness to participate in ABPM, time of measurement, number of canceled examinations, time to cancelation)

Objectives with longitudinal resultsDoes 24-h ABPM predictAll-cause mortalityCardiovascular mortalityDeath from infectionHospitalizations due toi.Cardiovascular eventsii.Infectious complicationsiii.Other reasons

Compare the predictive value of intradialytic BP measurements with 24-h ABPM

### Pulse wave analysis

Objectives with cross-sectional resultsEstablish a reference database for end stage renal disease patients in terms of central blood pressure valuesCorrelate measures of central hemodynamics with end organ damageFind associations between cardiovascular risk factors and measures of central hemodynamicsFind associations between volume depletion within the dialysis session and changes in central hemodynamics

Objectives with longitudinal resultsDoes 24-h PWA predictAll-cause mortalityCardiovascular mortalityDeath from infectionHospitalizations due toi.Cardiovascular eventsii.Infectious complicationsiii.Other reasons

Compare the predictive value of intradialytic PWA measurements with 24-h PWAEvaluate longitudinal changes in PWA

### Pulse wave velocity (derived mathematically from PWA measurements)

Objectives with cross-sectional resultsEstablish a reference database for PWV in an end stage renal disease cohortCorrelate PWV with end organ damageFind associations between PWV and other cardiovascular and functional variables (e.g. retinal vessel parameters, cardiovascular risk factors, inflammatory biomarkers, neurocognitive score)Associate PWV with end organ damage

Objectives with longitudinal resultsDoes 24-h PWV predictAll-cause mortalityCardiovascular mortalityDeath from infectionHospitalizations due toi.Cardiovascular eventsii.Infectious complicationsiii.Other reasons

Compare the predictive value of intradialytic PWA measurements with 24-h PWVEvaluate the progression of arterial stiffness overtime

### Static and dynamic retinal vessel analysis (RVA)

Objectives with cross-sectional resultsEvaluate the feasibility of this method in dialysis centers and a dialysis cohort (% inclusion, technical feasibility…)Establish a reference database for static and retinal vessel parameters in an end stage renal disease cohort and compare these with normal controls (controls already available for analysis)Correlate RVA parameters (static and dynamic) with end organ damageFind associations between static and dynamic retinal vessel variables and other cardiovascular and functional variables (cardiovascular risk factors, inflammatory biomarkers, neurocognitive score, central hemodynamics)

Objectives with longitudinal resultsDoes static or dynamic RVA predictAll-cause mortalityCardiovascular mortalityDeath from infectionHospitalizations due toi.Cardiovascular eventsii.Infectious complicationsiii.Other reasons

### Electrocardiogram (ECG)

Objectives with cross-sectional resultsEvaluate the feasibility of this method in dialysis centers and a dialysis cohort (% inclusion, technical feasibility, % of data sets reaching the quality to be included in the analysis)Calculate the prevalence of atrial fibrillation (first detected, paroxysmal, persistent, permanent) over 24 hDetermination of autonomic dysfunction with linear and non-linear methods and association of these parameters with end organ damage and cardiovascular risk factorsEvaluate the data set for new determinants of cardiac autonomic dysfunctionCalculate ECG parameters of hypertrophy and associate with end organ damageEvaluate for arrhythmias other than atrial fibrillation (ventricular tachycardia, ventricular extra systole, supraventricular extra systole)Evaluate basic ECG parameters (QRS duration, QT time, PR time, resting heart rate)Find associations between volume depletion within the dialysis session and changes in heart rhythm (arrhythmias including atrial fibrillation)

Objectives with longitudinal results

Does autonomic dysfunction at baseline predictAll-cause mortalityCardiovascular mortalityDeath from infectionHospitalizations due toCardiovascular eventsInfectious complicationsOther reasons

### Neurocognitive testing

Objectives with cross-sectional resultsEvaluate the feasibility of neurocognitive testing in a dialysis settingEvaluate the prevalence of cognitive impairment and dementiaAssociate neurocognitive scores with end organ damage and cardiovascular risk factorsAssociate vascular parameters (retinal vessel analysis for microcirculation, PWA and PWV for large vessels) with neurocognitive scores

Objectives with longitudinal resultsDoes cognitive impairment or dementia at baseline predictAll-cause mortalityCardiovascular mortalityDeath from infectionHospitalizations due toi.Cardiovascular eventsii.Infectious complicationsiii.Other reasons

Evaluate the progression of neurocognitive decline

### Cardiovascular risk stratification

After evaluation of the above data sets and risk stratification by single estimators we aim at building a multivariable Cox-Regression model which will include up to 15 variables depending on the number of cardiovascular events recorded throughout the observation period and the true number of recruited patients (see section on sample size and statistical analysis).

## Methods and design

Substantial requirements for the selection of technical examinations of the cardiovascular system were that they had to be (1) well validated, (2) feasible in daily practice and (3) cost efficient to allow use in a broad set of patients. What methods did fulfill the above mentioned criteria? The steering committee decided to use (1) 24-h Holter ECG, (2) 24-h ABPM and (3) retinal vessel analysis (RVA), as these methods give an excellent estimate of the situation in the macro- and microcirculation and all methods have been very well validated in the last years. As functional parameter of cerebrovascular microcirculation we aim to measure in parts of the cohort the neurocognitive status by Montreal Cognitive Assessment (MoCA) and Clinical Dementia Rating (CDR).

### Study design

The ISAR study is planned as a prospective, strictly observational cohort study conducted in dialysis centers in Munich and the greater Munich area (17 study sites). The Ethics Committee of the Klinikum rechts der Isar of the Technical University Munich and the ethics Committee of the Bavarian State Board of Physicians approved the study protocol. Informed consent is obtained from all patients. An overview of the examinations and follow up appointments can be found in Table 1.

**Table 1 Tab1:** Schedule of measurements and activities by visit for the ISAR study

	Baseline examination	Follow-up (FU) visits	
	T O (inclusion in the study)	T 24 months	T 6y
Interviewer/Questionaires			
Informed consent	X		
contact information	X	X	X
sociodemographic	X	X	X
Education and employment	X	X	X
Vascular access	X	X	X
Residual kidney function	X	X	X
Dialysis prescription	X	X	X
medical history	X	X	X
cardiovascular risk factors	X	X	X
Family history of CVD	X	X	X
history of prior transplantations	X	X	X
Physical activity	X	X	X
MOCA	X	X	X
CDR	X	X	X
Restless legs score	X	X	X
Oral medications	X	X	X
Examination			
Height, weight, BMI, upper arm circumference	X	X	X
Blood pressure	X	X	X
Procedures			
12-lead holter ECG (24h)	X		
24-h holter blood pressure	X		
Pulse wave velocity (single measurement)		X	X
Pulse wave analysis (single measurement)		X	X
Pulse wave velocity (24h)	X		
Pulse wave analysis (24h)	X		
Retinal vessel analysis (static examination)	X		
Retinal vessel analysis (dynamic examination)	X		
Blood tests (prior to dialysis, fasting), midweek dialysis session			
Serum blood sampling (frozen at −80 °C)	X	X	X
EDTA blood sampling (frozen at −80°)	X	X	X
Clinical follow up			
Hospitalizations (cardiovascular, infectious…)		X	X
cardiovascular events		X	X
cardiovascular mortality		X	X
total mortality		X	X
dialysis routine blood work (quarterly)			
Glucose, albumin	X	X	X
complete blood count	X	X	X
Electrolytes (Na, K, Mg, Ca, Phos)	X	X	X
Blood gas analysis	X	X	X
intact PTH	X	X	X
Iron status	X	X	X
Kt/V	X	X	X
Dialysis treatments			
Dry weight	X	X	X
dialysis prescription (duration, frequency, dialyzer)	X	X	X
Pre- and Post weights	X	X	X
Dialysis flow rates	X	X	X
Blood flow rates	X	X	X
intravenous medications within dialysis session	X	X	X

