#### Pulse wave analysis/central hemodynamics

Arterial stiffness as a sign of vascular calcification is a hallmark finding in patients with chronic kidney disease and especially end stage renal disease patients [58]. Estimation of vascular calcification can be performed either directly by imaging coronary calcification [59] or indirectly by monitoring arterial stiffness by (1) determining pulse wave velocity [60] by measuring pressure wave at two sites (common carotid and femoral artery) and calculation of the time delay of both pressure curves or by means of (2) pulse wave analysis where the brachial pulse wave is mathematically transferred into an aortic pulse wave which can be used to derive PWV values in m/s [10, 61]. The huge advantage of using the latter method is the chance to use 24-h pulse wave analysis and not only a single measurement [10]. This is especially important as pulse wave curves change with volume shifts during and in the period after the dialysis procedure [13]. This method has been very well validated in the last years not only in normal subjects [10] and cardiovascular risk cohorts [11, 62] but also in CKD [18] and dialysis patients [13]. Another advantage is the user independency of the method which would allow broad application in dialysis centers, because “classical” measurement of PWV needs an experienced examiner and is time consuming. Therefore, PWV measurement has not entered clinical routine use except in specialized academic centers within study protocols.

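### PWV and PWA are scheduled as 24-h recordings at baseline but as single measurements at 24 months and 6 years, so baseline-to-follow-up change mixes progression with a change of measurement mode

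*Protocol article*

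**What the plan says.** In the protocol article, Study design, Table 1 (Procedures), the rows "Pulse wave velocity (24h" and "Pulse wave analysis (24h" are marked at baseline and nowhere else. The rows "Pulse wave velocity (single measurement" and "Pulse wave analysis (single measurement" are blank at baseline and marked at 24 months and 6 years.

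The abstract (Methods/design) gives the same schedule in prose. Baseline includes "24 h pulse wave analysis (PWA) and pulse wave velocity (PWV", and then: "After 24 months biochemistry and determination of single PWA, single PWV and neurocognitive testing are repeated". The single measurements are thus described as a repeat, although none is scheduled at baseline.

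Change over time is a stated aim. Study objectives lists following arterial stiffness and central hemodynamics over time among the main goals. The PWA and PWV objective sections each add a longitudinal item, on changes in PWA and on progression of stiffness.

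Study procedures/measurements starts the 24-h blood pressure recording shortly before a midweek dialysis session. The methods section on ABPM and pulse wave analysis says the stiffness parameters are recorded over the same 24 hours.

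**The concern.** A change score needs the same quantity at both visits. Here the baseline quantity is a profile running from shortly before dialysis through the session and the hours after it. The follow-up quantity is one reading. No visit schedules both modes, so from baseline to either follow-up the mode is fully confounded with the visit.

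The article itself gives a reason to doubt that the two agree. In the Discussion (Pulse wave analysis/central hemodynamics) it presents as an advantage "the chance to use 24-h pulse wave analysis and not only a single measurement", and explains: "This is especially important as pulse wave curves change with volume shifts during and in the period after the dialysis procedure".

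At stake is one of the stated main goals. If the two modes differ systematically, the difference would be reported as progression or regression of stiffness, and recruiting more patients would not remove it.

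**Working it through.** **Is the schedule read correctly?** Yes. Table 1 and the abstract state it independently and agree, so it is not a table broken in extraction.

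**Which comparisons are affected?** Let δ be the true mean change and b the mean difference between a single reading and the 24-h summary under the same conditions.

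| Comparison | Modes | Expected observed change |
|---|---|---|
| Baseline to 24 months | 24-h, then single | δ + b |
| Baseline to 6 years | 24-h, then single | δ + b |
| 24 months to 6 years | single, then single | δ (no mode term) |

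Prediction of events from the baseline 24-h value uses one mode throughout, so b does not enter.

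**How large could the effect be?** The article gives no figure for PWV or PWA change, so there is none to reproduce. It also gives no offset and no SD. The following is illustration only.

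Inputs:
- Pairs, upper end: Sample size gives 500 patients and 20 % two-year mortality, so 500 × (1 − 0.20) = 400 survivors at 24 months. This is an upper bound, because Screening and eligibility requires only one of the three technical examinations, so some patients may have no baseline PWV or PWA.
- Pairs, lower end: 200, assumed.
- SD of the change: 1.0 to 1.5 m/s, assumed.
- Offset b: 0.1 or 0.2 m/s, assumed.
- True change: δ = 0.
- Test: two-sided 5 %, as in Statistical analysis.

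Formulas: SE = SD/√n, and P(significant) = 1 − Φ(1.96 − b/SE) + Φ(−1.96 − b/SE).

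| Pairs | SD (m/s) | SE (m/s) | b = 0.1 m/s | b = 0.2 m/s |
|---|---|---|---|---|
| 400 | 1.0 | 1.0/20 = 0.050 | 52 % | 98 % |
| 400 | 1.5 | 1.5/20 = 0.075 | 27 % | 76 % |
| 200 | 1.0 | 1.0/14.14 = 0.071 | 29 % | 81 % |
| 200 | 1.5 | 1.5/14.14 = 0.106 | 16 % | 47 % |

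With no offset, each entry would be 5 %. The estimate itself is biased by b in every row. Sample size changes only how often that bias is declared significant.

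**The case against.** The strongest reply is that the article never says how change will be computed. A reader might infer from the schedule that the plan is to subtract the 24-h mean from the single follow-up value, but no sentence says so. A 24-h recording is a series of readings, and the article already intends to use parts of it: the PWA and PWV objectives compare intradialytic readings with the 24-h values. A pre-dialysis baseline reading is probably available, and calling the follow-up measurements a repeat is compatible with using one. The choice of comparator and the timing of the follow-up reading may also be settled in a full protocol or analysis plan that is not shown. All of this stands, and the absence of those details from the article is not the point here. The point is the schedule that the article does state, which leaves the two visits non-comparable unless a matched baseline value is chosen.

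A reader might also infer that every longitudinal PWV or PWA result is compromised. It is not: the comparison of 24 months with 6 years is single against single and serves the same objectives. It says nothing, however, about the first two years and is limited to patients who reach both later visits.

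Finally, the probabilities rest on assumed offsets and SDs, and the true offset could be near zero or of either sign. That stands too. The figures show that a small offset would matter; they do not show that one exists.

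**Conclusion.** The concern holds for change from baseline to 24 months and from baseline to 6 years. For these comparisons the scheduled values cannot separate progression from mode, and the article's own remarks on volume shifts around dialysis mean that equivalence cannot be taken for granted. Size and direction of the offset cannot be derived from the document. Under the assumptions above, a pure artefact of 0.1 m/s would reach significance with probability of about 16–52 %, and one of 0.2 m/s with about 47–98 %.

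The severity is moderate. A main goal is touched, but the mortality sample size, the prognostic Cox model and prediction from baseline 24-h values are not. The data are probably recoverable from recordings already made. The document does not support the stronger conclusion that the stiffness data are unusable, or that a biased change score has been planned.

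**What to change.** 1. For analyses of change from baseline, define the baseline comparator as the reading or readings in the existing 24-h recording that match the follow-up single measurement in number and in timing relative to the midweek dialysis session, for example those taken before the session starts.
2. Take the follow-up reading at that same point with the same device, or confirm that the full protocol already says so.
3. Do not use the 24-h mean as the baseline for change. Keep it as a baseline predictor of outcome.
4. Report the change from 24 months to 6 years separately, as the comparison in which the mode does not change.

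The Conclusion section says that recruitment is finished, so a separate single reading at baseline can no longer be scheduled; extraction from the recordings is the practical route. The cost is that extraction and a line in the follow-up procedure. The downside is that one or a few baseline readings are noisier than a 24-h mean, so the change estimate loses some precision in return for removing the mode offset.
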